## Abstract

**Background:**

Transgender and gender nonconforming people experience some of the highest human immunodeficiency virus (HIV) rates in the United States, and experience many structural and behavioral barriers that may limit their engagement in HIV testing, prevention, and care. Evidence suggests that transgender and gender nonconforming youth (TY) are especially vulnerable to acquiring HIV, yet there is little research on TY and few services are targeted towards HIV testing, prevention, and care for this population. Telehealth presents an opportunity to mitigate some structural barriers that TY experience in accessing HIV testing, allowing TY to engage in HIV testing and counseling in a safe and nonjudgmental space of their choosing. Project Moxie is an HIV prevention intervention that pairs the use of HIV self-testing with remote video-based counseling and support from a trained, gender-affirming counselor. This study aims to offer a more positive HIV testing and counseling experience, with the goal of improving HIV testing frequency.

**Objective:**

Project Moxie involves a pilot randomized controlled trial (RCT) of 200 TY aged 15-24 years, who are randomized on a 1:1 basis to control or intervention arms. The aim is to examine whether the addition of counseling provided via telehealth, coupled with home-based HIV testing, can create gains in routine HIV testing among TY over a six-month follow-up period.

**Methods:**

This study implements a prospective pilot RCT of 200 TY recruited online. Participants in the control arm will receive one HIV self-testing kit and will be asked to report their results via the study’s website. Participants in the experimental arm will receive one HIV self-testing kit and will test with a remotely-located counselor during a prescheduled video-counseling session. Participants are assessed at baseline, and at three and six months posttesting.

**Results:**

Project Moxie was launched in June 2017 and recruitment is ongoing. As of August 21, 2017, the study had enrolled 130 eligible participants.

**Conclusions:**

Combining home-based HIV testing and video-based counseling allows TY, an often stigmatized and marginalized population, to test for HIV in a safe and nonjudgmental setting of their choosing. This approach creates an opportunity to reduce the high rate of HIV among TY through engagement in care, support, and linkage to the HIV treatment cascade for those who test positive.

**Trial Registration:**

ClinicalTrials.gov NCT03185975; https://clinicaltrials.gov/ct2/show/NCT03185975 (Archived by WebCite at http://www.webcitation.org/6vIjHJ93s)

## Introduction

Evidence increasingly suggests a high prevalence of human immunodeficiency virus (HIV) infections among transgender and gender nonconforming individuals in the United States [1]. Recent studies, drawn largely from samples of transgender women, suggest the prevalence of HIV in this population is at least as high as that experienced by gay, bisexual, and other men who have sex with men (MSM) [2-4]. A 2013 report found that the estimated percentage of transgender women living with HIV in the United States was 22% [4], and among the 3.3 million HIV testing events reported to the Centers for Disease Control and Prevention (CDC) in 2013, the percentage of transgender people who received a new HIV diagnosis was more than three times the national average [1]. Transgender women of color and those under 25 years of age are disproportionately affected by the HIV epidemic [5,6].

Much of what is known about HIV risk behaviors among transgender and gender nonconforming people has been derived from samples of transgender women [1]. The high rate of HIV in this population has been associated with a high prevalence of substance abuse, commercial sex work, condomless anal intercourse, and a lack of knowledge regarding HIV transmission [5,7-10]. While data on other transgender and gender nonconforming populations is sorely lacking, many of the risk factors for HIV seen in transgender women are shared by other groups of transgender and gender nonconforming people, and the prevalence of HIV is thought to be similar across transgender and gender nonconforming populations [3]. While transgender and gender nonconforming youth (TY) are even more underrepresented in the literature, available research from a sample of trans-feminine youth shows that this population experiences multiple forms of discrimination and harassment, significantly increasing the risk of HIV transmission [11,12]. A study of 51 ethnic-minority, female-identifying TY showed higher rates of HIV compared to other racial/ethnic groups, with 41% experiencing difficulty accessing health care, 59% reporting engaging in transactional sex, and 63% reporting difficulty finding employment [9].

Telehealth uses short message service (SMS) messaging, teleconferencing and videoconferencing platforms, social media, and smartphone apps compliant with the Health Information Portability and Accountability Act (HIPAA) to increase access to health care [13]. Given the multiple barriers to accessing HIV prevention and care experienced by transgender and gender nonconforming people, telehealth may be a useful platform for delivering services directly to these populations. Due to high rates of technology use among youth [14], telehealth may be especially useful for addressing the discrimination and harassment TY encounter while attempting to access health care resources [15,16]. Telehealth may also provide an entry point to the health care system in places where no gender-affirming providers or services exist.

Telehealth has already been adapted to provide HIV care services to MSM residing in areas where stigma and minimal lesbian, gay, bisexual, transgender (LGBT)-friendly health care providers exist [17]. SMS-based telehealth efforts have also been implemented to connect MSM in metropolitan Kansas City with an HIV testing counselor to increase the dissemination of evidence-based HIV/sexually transmitted infection (STI) prevention information [18]. Telehealth-based interventions have also been used among rural HIV-positive veterans in the United States, wherein they participated in private teleconferences with HIV specialists [19]. This intervention was shown to increase the veterans’ perceptions of the quality of care provided, and was considered a step towards reducing HIV risk behaviors such as condomless intercourse and multiple sexual partners [19]. While telehealth-based interventions may reduce the stigma associated with in-person appointments by allowing rural MSM and HIV-positive veterans to access services in a place where they feel comfortable, research has not focused on the use of telehealth to provide HIV prevention resources to other marginalized populations, such as TY.

Another important limitation of the current telehealth literature concerns its use as an information dissemination and case management tool. Few studies use this technology for actual clinical care, such as HIV testing. With approval by the US Food and Drug Administration in 2011, high quality (sensitivity 93.64%, 95% CI 82.46-98.66; specificity 99.87%, 95% CI 99.28-100.00 [20]), home-based HIV testing is now available commercially in all 50 states [21]. However, critiques of home-based HIV testing include difficulty interpreting the results, a lack of posttest counseling for the adoption of safer HIV prevention methods, and a lack of proper linkage to care [22]. Adding online counseling through video-chat software to home-based HIV testing has the potential to mitigate these concerns. Through telehealth-delivered counseling, individuals can receive tailored, convenient, and confidential support that due to stigma, discrimination, and/or lack of locally-available services, may not otherwise be received. While there are few telehealth-based HIV prevention interventions published in the literature, results from prior studies show increased knowledge, self-efficacy, and motivation towards effective HIV prevention methods [23-26].

This paper describes the protocol for the first study to combine telehealth and home-based HIV testing for comprehensive, gender-affirming HIV testing and counseling for TY. In this study, approximately 200 TY aged 15-24 years will be randomized into either a control group that receives an HIV self-testing kit or an intervention group that receives an HIV self-testing kit as well as a video-chat counseling session provided by a trained HIV counselor. The main outcome of this study is the frequency of HIV testing in the six months following initial testing. The study aims to examine whether the receipt of an HIV self-testing kit plus a video-chat-delivered counseling session can create changes in HIV testing behavior, sexual risk-behaviors, and linkage to care for newly-diagnosed HIV-positive TY. If successful, this low-cost intervention has the potential to shape the delivery of HIV prevention and care services to this population, who are currently overlooked in HIV programming, research, and prevention efforts.

## Methods

### Study Overview

This study is a pilot randomized controlled trial (RCT) of 200 self-identified TY aged 15-24 years, recruited via a range of social media platforms. Participants will be randomized to one of two study arms. TY in the control arm will receive one HIV self-testing kit by mail and will be asked to report their results via a study website. TY in the experimental arm will also receive one HIV self-testing kit via mail, and will conduct this test under the supervision of a remotely-located counselor during a prescheduled video-chat session. Participants in both arms will complete a baseline survey upon recruitment, with repeat surveys at three and six months posttesting (see Figure 1). Participants will receive email and SMS reminders to log into the study website to complete follow-up surveys. The primary outcome for this study is routine HIV testing during the follow-up period. Secondary outcomes include sexual risk-taking behaviors, intervention acceptability, and linkage to care for those who test positive for HIV.

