### Study Procedure

After providing consent electronically, participants will be directed to a short eligibility screener. If eligible, a potential participant will register for the study by providing their contact information. This information includes an email address, mobile phone number, physical mailing address, and preferred choice of name and pronouns. It is important to note that many TY have unstable housing or may not feel comfortable having mail, however discreet, sent to their home address. For this reason, the registration form will ask for a physical address to which the participant feels safe and comfortable receiving mail. As soon as the consent form, screening questionnaire, and site registration are complete, the participant will receive an email with instructions on completing the baseline survey. After completing the baseline survey, each participant will be randomized to either the control arm (HIV self-testing only) or intervention arm (video-based counseling in conjunction with HIV self-testing), using a 1:1 treatment allocation. The treatment assignments will be generated with the use of a pseudo-random number generator, which uses permutated blocks to ensure balance in the number of participants assigned to each arm. The randomization process will generate one of two emails to study participants, indicating whether they will be receiving HIV self-testing or video-based counseling plus HIV self-testing.

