### Statistical Analysis

The primary outcome will be the proportion of TY who tested for HIV at least once in the six-month follow-up period. Descriptive statistics of participant characteristics will be presented for all participants and also by study arm. These results will be compared using student t-tests or Wilcoxon rank sum tests for continuous variables, and Chi-square tests for categorical variables. The analysis for each outcome measure is described in detail below.

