## Results

Project Moxie began recruitment on June 19, 2017 and has enrolled 130 participants as of August 21, 2017. Self-testing kits have been mailed to a total of 71 participants. Video-chat sessions for 12 participants randomized to the experimental arm have been completed and 58 participants from the control arm have entered their test results into the study database.

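### Surveys and the six-month outcome window are timed from the initial test, which follows randomization and is reached differently by arm, so participants who never test have no defined follow-up

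*Protocol article*

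**What the plan says.** **Order of events.** Under Study Procedure: "After completing the baseline survey, each participant will be randomized to either the control arm (HIV self-testing only) or intervention arm". The same section sets the ratio, "using a 1:1 treatment allocation". The kit is mailed and used only after that.

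**Start of follow-up.** Study Overview: "Participants in both arms will complete a baseline survey upon recruitment, with repeat surveys at three and six months posttesting". The Abstract (Methods) agrees: "Participants are assessed at baseline, and at three and six months posttesting". The Introduction ties the outcome to the same event: "The main outcome of this study is the frequency of HIV testing in the six months following initial testing".

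**Primary outcome in the analysis section.** Statistical Analysis: "The primary outcome will be the proportion of TY who tested for HIV at least once in the six-month follow-up period". No other starting point is given there, so the three places above are the only definition of when follow-up begins.

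**How each arm reaches the initial test.** Control participants test themselves and enter the result on the website (Control Arm). Intervention participants leave the package sealed, install the video software and test only during the scheduled session (Study Overview; Intervention Arm).

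**Progress to 21 August 2017.** The Results section counts 130 people enrolled and 71 kits sent out, without a split of the kits by arm. On initial tests it reports: "Video-chat sessions for 12 participants randomized to the experimental arm have been completed and 58 participants from the control arm have entered their test results".

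**The concern.** A randomized comparison is protected when the clock starts at randomization, or at an event that the assigned arm cannot influence. Here it starts at something the participant does after learning the assignment, and one arm has more steps to complete first. The event is itself an HIV test, so whether it happens is likely to be related to the outcome, which is later HIV testing.

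Two things follow. A participant who never takes the initial test has no dates from which to schedule surveys or count six months. Among those who do test, the window opens at a delay from randomization that depends on arm. The sexual-risk analysis uses the same follow-up, through person-years and three-month counts.

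The survey schedule is data collection. An analysis plan can define who is analysed, but it cannot recover surveys that were never sent.

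**Working it through.** The plan gives no figure for this point. The check is the order of events, then the progress counts, then an illustration.

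**1. Who has a window under the stated timing**
- Tests *d* months after randomization: surveys fall at *d* + 3 and *d* + 6 months, and the outcome window runs from *d* to *d* + 6.
- Never tests: *d* does not exist, so there are no survey dates and no window. The article gives no rule for this case.
- *d* includes dispatch and self-testing in control; in intervention it also includes software set-up, scheduling and attendance.

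**2. What the counts fix** (inputs from Results; every reported test is taken to have used a mailed study kit)
- Control kits mailed: at least 58. Intervention kits mailed: at most 71 − 58 = 13.
- Intervention kits mailed: at least 12. Control kits mailed: at most 71 − 12 = 59.
- Use per kit mailed: control 58/59 to 58/58 = 98% to 100%; intervention 12/13 to 12/12 = 92% to 100%.

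**3. What the counts suggest per randomized participant** (needs an assumption)
- If all 130 enrolled had been randomized, about 65 per arm: control 58/65 = 89%; intervention 12/65 = 18%.
- If only about 58 per arm had been randomized, the fewest compatible with 58 control results and balanced blocks: control 58/58 = 100%; intervention 12/58 = 21%.

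On either assumption the arms differed greatly in how many had a time zero. By step 2, the gap arose before mailing, not between mailing and use.

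**4. Illustration of a testers-only comparison with no true effect** (all inputs assumed)

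Suppose the chance of later testing falls linearly from 50% in the most motivated to 10% in the least, and the most motivated take the initial test first. If a fraction *f* of an arm tests, the mean among testers is 50 − 20*f* (in %). Control at *f* = 0.89 gives 50 − 17.8 = 32.2.

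| Intervention *f* | Intervention testers | Spurious difference |
|---|---|---|
| 0.18 (12/65) | 46.3 | about 14 points |
| 0.40 | 42.0 | about 10 points |
| 0.60 | 38.0 | about 6 points |
| 0.80 | 34.0 | about 2 points |

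Counting everyone randomized gives 50 − 20 = 30% in both arms. The smallest difference for which the Sample Size section states power is 10 points. If entry were not ordered by motivation, the distortion could be smaller or take the opposite sign.

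**5. What moving the clock must not do**

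A window opening at randomization contains the study-supplied test. If that test counted, step 3 shows 89% of control and 18% of intervention already classed as having tested (65 per arm assumed). The HIV Testing measures ask about tests since the last survey, and for the month-3 survey the last survey is baseline. That recall period therefore already spans the initial test, and the exclusion has to be written down.

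**The case against.** Four counter-arguments deserve weight.

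- **The analysis is not restricted to testers.** A reader might infer that the trial compares self-selected testers. The HIV Testing analysis refers to participants in each arm and writes no such restriction, and handling of non-starters may sit in a plan not shown. This stands: the restriction follows only if surveys are triggered by a test.
- **The outcome can be measured without an initial test.** Follow-up surveys ask about testing since the last survey. This also stands, but a survey with no due date is not sent, so the gap in the schedule remains.
- **The counts are from mid-recruitment.** A reader might infer that intervention participants refuse to test, or that allocation was not 1:1. Neither is shown. Nearly every mailed kit was used in both arms, enrolled need not mean randomized, and nothing says kits were dispatched without regard to arm. Scheduling lag and non-uptake look the same here, and final uptake is unknown.
- **The bias figures are assumed.** Correct. They show what could happen, not what did, and a reader should not infer that the intervention arm is necessarily favoured.

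None of these supplies a survey date for a participant who never tests, or removes the arm-dependent delay.

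**Conclusion.** The concern holds as a flaw in how follow-up is timed. From the wording alone, the time origin comes after randomization, the arms reach it by different routes, and a participant who never takes the initial test has no survey dates and no outcome window. This needs no assumption beyond following the stated schedule.

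The size and direction of any bias cannot be determined. Under the assumed motivation gradient, a testers-only comparison with no true effect would be off by about 2 to 14 points for intervention uptake of 80% down to 18%. The August 2017 counts show that entry was then far slower or rarer in the intervention arm (at most 13 of 71 kits; 12 sessions against 58 results), but not why. The trial is a pilot, yet the timing should be corrected before follow-up surveys fall due, because lost data cannot be restored in the analysis.

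**What to change.** - Send the month-3 and month-6 surveys on a calendar that starts at randomization for everyone, whether or not the kit was used or the session held.
- Analyse all randomized participants in their assigned arm over that fixed six-month window.
- State that the study-supplied initial test does not count towards the primary outcome, and word the survey item so that it can be told apart from later tests.
- Keep the six months after the initial test as a supportive analysis.
- Report kits mailed, kit use and session attendance by arm, with time from randomization.

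**Cost.** A changed survey trigger and revised outcome wording; no added participants or procedures. Recruitment began on 19 June 2017, so no one could have reached three months from enrolment by the 21 August count. At that date the new calendar would have missed no survey.

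**Downside.** Someone who tests *d* months after randomization has 6 − *d* months of post-test time in the window. Late testers are more likely in the intervention arm, so its time after counselling is somewhat shorter. The supportive analysis shows how much this matters.

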### Participants

Eligible participants will: (1) be aged 15-24 years; (2) have not tested for HIV in the last 12 months; (3) reside in the United States; (4) be willing to have HIV test kits delivered to an address they provide, (5) self-identify as noncis-gender; and (6) have access to a computer, smartphone, or tablet that can support the video-chat software VSee [27], which is an encrypted program compliant with the privacy requirements of the HIPAA.

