Phase two of the session will consist of testing for HIV. Prior to the test, counselors will offer standard content for risk elicitation and identification of safer sex goal behaviors. The participant, directed by the counselor, will conduct their own test and read their own results. They will then show the counselor their test result for confirmation. Based on the results of the test and the information gathered in phase one, the counselor will assist the participant in developing a prevention or care plan to reduce the risk of acquiring or transmitting HIV (eg, number of sexual partners, frequency of unprotected intercourse). The counselor will describe the behavioral and biomedical interventions appropriate for each participant, such as condom use, partner reduction, decreasing drug or alcohol use, and/or preexposure prophylaxis (PrEP). At the end of the video-chat session, participants who show a positive result will be counseled on the need for timely confirmatory testing and linkage to care. The counselor will arrange a time within one week of the initial session to conduct a second video-chat session. During the second session, the counselor will determine other resources from which the participant may benefit, such as medical case management, mental health care, and/or more comprehensive psychological counseling and services. TY who test positive will also be directly linked to medical care in the second session by connecting them with a provider in their local area or another area designated by the participant. Study staff will follow up on the next business day to ensure that contact was made with the participant’s desired facility. The participant will be contacted at least three more times: (1) to confirm an appointment was scheduled, (2) to confirm that the appointment was attended, and (3) to report confirmatory test results.

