#### Outcomes

The primary outcome for this study is routine HIV testing, defined as testing at least once during the follow-up period (ie, every 3-6 months) based on the HIV risk profile of the participant. Secondary outcomes consist of sexual risk-taking behaviors, intervention acceptability at the final survey, and linkage to HIV care (for those who report a positive result at baseline or during the course of the intervention). Key covariates include measures of transphobia and social marginalization.

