#### HIV Testing

History of HIV testing, including measures of frequency, place of testing, method of testing, and linkage to care (if HIV-positive), will also be collected at baseline. Follow-up surveys will repeat the questions from the baseline and will also ask questions regarding HIV testing since the last survey. These parameters include location of test (eg, home, Acquired Immunodeficiency Syndrome Service Organization, Department of Public Health, or physician), test result, care received (specifically for HIV-positive participants), and reason for testing (ie, routine care versus episodic exposure).

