#### Linkage to Care

It is important to introduce participants whose self-tests are positive to the HIV treatment cascade and continue following-up on their HIV testing frequency, sexual risk behaviors, and experiences with HIV stigma and transphobia. Per the recent recommendations of the Institute of Medicine [47], indicators of linkage to care will include: (1) attending at least one clinical care appointment, (2) having at least one CD4 test performed, and (3) having at least one viral load test performed within three months of HIV diagnosis [32,48].

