#### Sexual Risk-Taking

Sexual risk behavior will be defined as any unprotected anal or vaginal intercourse that occurs during the follow-up period with a person who is known by the participant to be HIV-positive, or has an unknown serostatus. The incidence of at-risk sex acts will be calculated as an incidence density, with the numerator being number of individual at-risk sex acts, and the denominator being person-years of follow-up time. Comparisons of the incidence of unprotected sex will be made by comparing incidence densities across arms. Incidence rates per person-year of follow-up will be estimated and compared using methods based on the Poisson distribution and using the generalized estimating equation (GEE) approach. Key covariates include demographic characteristics, previous HIV testing history, and reported stigmas and transphobia. Period incidence rates (three-month incidence density rates) of at-risk sex will be estimated by performing a GEE Poisson regression analysis of the trimonthly counts, implemented using SAS PROC GENMOD [49]. GEE models will control for demographic characteristics, baseline HIV testing history, and stigma, and will also be used to examine interactions between forms of stigma (HIV and transphobia) and sexual risk-taking.

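### HIV status enters neither the eligibility list, the primary outcome rule nor the at-risk act rule, so outcomes of known and newly found positives are misclassified

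*Protocol article*

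**What the plan says.** All places are in the protocol article.

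- **Participants.** Six criteria are listed. The only one on testing is that people "have not tested for HIV in the last 12 months". None concerns HIV status.
- **Measures, HIV Testing.** The survey item on "linkage to care (if HIV-positive), will also be collected at baseline". Follow-up surveys ask for location, result and reason for each test; the reasons named are routine care and episodic exposure.
- **Outcomes.** Routine testing is defined as at least one test in follow-up, in light of the participant's risk profile. Linkage to care is a secondary outcome "for those who report a positive result at baseline or during the course of the intervention".
- **Statistical Analysis.** The primary outcome is "the proportion of TY who tested for HIV at least once in the six-month follow-up period". The Introduction starts the six-month window at the initial test.
- **Control Arm.** After a reported positive result, staff call to offer information on confirmatory test sites, care services and counseling.
- **Intervention Arm.** After a positive result there is counseling on confirmation, a second video session within a week, a next-business-day check and at least three further contacts, the last listed as "3) to report confirmatory test results".
- **Measures, Linkage to Care.** For participants with a positive self-test the study will "continue following-up on their HIV testing frequency, sexual risk behaviors, and experiences with HIV stigma and transphobia".
- **Sexual Risk-Taking.** An at-risk act is unprotected intercourse "with a person who is known by the participant to be HIV-positive, or has an unknown serostatus".

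**The concern.** Three stated rules ignore the participant's HIV status.

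1. **Eligibility.** A person with an established diagnosis has no reason to retest and so meets the testing criterion. Neither the first counseling phase, which explores why the person has not tested, nor the primary outcome has meaning for them.
2. **Primary outcome.** Any test inside the window counts. A confirmatory test after a reactive kit falls inside it, yet it is follow-up of a result, not the gain in routine testing that the trial aims to show. Because staff pursue confirmation with different intensity in the two arms, study activity can feed the primary endpoint unequally.
3. **Sexual risk.** Positives stay under follow-up for sexual risk, and the intervention's prevention or care plan covers transmission as well as acquisition. The act rule is written for acquisition only.

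At stake are a small dilution of the primary comparison, a possible shift in favor of the intervention, and misclassified acts among the participants who could transmit.

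**Working it through.** **Primary outcome.** The documents give no number of positives and no confirmation rates, so all of the following are assumptions:

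- q, the share newly positive in each arm: 1% to 5%. Of 200 completers that is 200 × 0.01 = 2 to 200 × 0.05 = 10 people.
- c_I and c_C, the share of positives with a confirmatory test in the intervention and control arms: 90-100% and 50%.
- p, the testing rate among the others.

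The observed rate in an arm is (1 − q)p + qc. With no true effect and equal q, the terms in p cancel and the spurious difference is q × (c_I − c_C):

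| q | 90% vs 50% | 100% vs 50% |
|---|---|---|
| 1% | 0.01 × 0.40 = 0.4 points | 0.01 × 0.50 = 0.5 points |
| 5% | 0.05 × 0.40 = 2.0 points | 0.05 × 0.50 = 2.5 points |

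The smallest difference in the Sample Size section is 10 points, so the range runs from 0.4/10 = 4% to 2.5/10 = 25% of it. That section's enrollment figure reproduces: 200/(1 − 0.20) = 250. Its power figures cannot be checked uniquely, because control rate, alpha and sidedness are not given; nothing here rests on them.

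If confirmation is equal in both arms, a true difference d becomes (1 − q)d: 10 points shrink to 9.9 at q = 1% and 9.5 at q = 5%. As an illustration, take 100 per arm, two-sided alpha 0.05, and 10% versus 20% testing among the others (power 50.8% with no positives):

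| q | Confirmatory tests counted, 90% in both arms | Not counted, positives kept as non-events |
|---|---|---|
| 1% | 10.8% vs 20.7%, power 48.5% | 9.9% vs 19.8%, power 50.3% |
| 5% | 14.0% vs 23.5%, power 40.5% | 9.5% vs 19.0%, power 48.5% |

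Not counting these tests removes the arm artefact and most of the power loss. The dilution by (1 − q) stays, because the positives remain in the denominator.

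**Direction.** If kits detect different shares q_I and q_C in the two arms, the spurious difference is q_I(c_I − p) − q_C(c_C − p). With p = 10%, 90% versus 50% confirmed, q_C = 5% and half that in the intervention arm, it is 0.025 × 0.80 − 0.05 × 0.40 = 0. A shift toward the intervention therefore requires roughly similar detection.

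**At-risk acts.** The rule applied to unprotected acts of an HIV-positive participant:

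| Partner | Counted by the plan | Relevant to transmission |
|---|---|---|
| Known positive | Yes | No |
| Known negative | No | Yes |
| Unknown | Yes | Yes |

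The rule fails for both kinds of known-status partner and agrees for unknown status.

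**The case against.** The strongest case against is that this is a small wording gap in a pilot.

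- **Few known positives.** Someone who knows they are positive has little reason to join a self-testing trial. The Introduction and the linkage analysis speak of newly diagnosed or newly identified people. The conditional baseline item may be an ordinary skip pattern, so it does not show that known positives are expected. This stands as an argument about size; the eligibility list still admits them.
- **Routine testing.** The Outcomes section calls the outcome routine, and the reason for each test is recorded. But routine is defined there as testing at least once, the reasons named do not include confirmation, and the analysis rule does not use the item. The detail of which tests count may be left to a statistical analysis plan, but the rule as stated admits any test.
- **Acquisition risk.** The act rule is coherent for a mostly negative or untested sample. That is so, and the misclassification concerns few people and a secondary outcome.

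Some stronger readings are tempting but unsupported:

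- A reader might apply the 22% in the Introduction, giving 200 × 0.22 = 44 positives and 0.22 × 0.40 = 8.8 points. That figure is for transgender women, not for youth aged 15-24 of all noncisgender identities untested for a year; it is at most an outer bound.
- A reader might take a quarter of the design difference as the expected artefact. It is the most extreme corner of the assumed range.
- A reader might infer that control positives get one call only. The article sets no such limit.
- A reader might call the at-risk rule fully reversed for positives. Acts with unknown-status partners count either way.
- A reader might conclude that the trial is biased toward the intervention. The Results section reports 12 completed video sessions against 58 control results entered; these early counts leave open that detection differs by arm.

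**Conclusion.** The concern holds in a limited form. As written, the rules admit people with a known diagnosis, score confirmatory tests as success, and classify a positive participant's acts with known-status partners wrongly. That newly positive participants stay in the analyses is not said outright; it follows from their continued follow-up and from denominators with no restriction by HIV status.

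The size is an assumption throughout: about 0.4-0.5 points at 1% newly positive and 2.0-2.5 points at 5%, with 90-100% versus 50% confirmed and similar detection in both arms. With equal confirmation there is dilution only. The number of positives is probably small, so the likely effect is modest. The point is worth acting on because the rules misclassify outcomes when followed as stated and are cheap to correct.

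**What to change.** 1. Add one screener item, self-reported: no prior HIV diagnosis. Recruitment was already under way, so for those enrolled exclude baseline-reported positives from the primary analysis, using only data recorded before randomization.
2. State that a confirmatory test after a reactive study kit does not count toward the primary outcome. Keep kit-detected positives in the randomized comparison and add a sensitivity analysis of how they are handled. Do not drop them: their status arises after randomization and is ascertained differently by arm (shown to a counselor versus self-entered), so dropping them could itself bias the comparison.
3. Define at-risk acts by the participant's own status at the time: for positives, condomless sex with a negative or unknown-status partner. Alternatively, restrict the sexual-risk analysis by baseline-reported status only, never by kit-detected status.

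These changes concern enrollment and scoring, not the support offered to people who test positive. Partner serostatus and test results are already collected. The cost is one screener item, two definitions, slightly more analysis work and a few participants fewer in the primary analysis.
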